## **1. SUMMARY**

The objective of this study is to validate the Remote Food Photography Method (RFPM) to assess food intake in formula fed infants. Up to 75 men and women will participate in this 2-week study. Participants will be asked to prepare, in random order, multiple servings of 2 fluid ounce, 4 fluid ounce, 6 fluid ounce and 8 fluid ounce bottles of infant formula on 2 occasions about 1 week apart.

In this observational study, we will test the primary aim to assess if the RFPM can accurately estimate simulated food intake compared to the gold standard– directly weighed foods. A secondary aim is to evaluate the inter- and intra- individual variability in infant formula preparation.

## **2. BACKGROUND AND SIGNIFICANCE**

### **2.1. Infant Food Intake**

Measuring food intake for infants is challenging because foods and eating patterns are constantly changing during the first two years of life. In addition, food intake during the first two years of life dramatically differs from food intake during the remainder of life, where most of the methods for assessing food intake are focused. Infants begin feeding with exclusively human milk or infant formula. Pureed foods and, then, solid foods are introduced gradually within the first year of life. Challenges and inconsistencies with measuring food intake in infants include losses from spit up and losses from infant movement. Test weighing is commonly used to measure food intake in early infancy as this method is believed to be the most accurate behind doubly labeled water. Test weighing involves weighing infants before and after an observed feeding with the difference in weight indicative of food intake. Test weighing may be used in infants that are breastfed and formula fed, but studies suggest it is most frequently used during early infancy. Twenty-four hour dietary recalls and the directly weighed food method are also commonly used to determine energy intake in infants and toddlers. A previous study in infants and toddlers showed that the directly weighed food method estimated energy intakes within 5% of estimated energy requirements and that the 24 hour dietary recalls overestimated energy intakes in infants by 13% and in toddlers by 29%. Research suggests that established methods for evaluating infant food intake are useful, but their limitations and challenges show a need for new methods to be developed and validated.

According to the Federal Food, Drug, and Cosmetic Act (FFDCA), infant formula should be used solely as food for infants as a complete or partial substitute for human milk. The majority of formula available in the United States is sold in powdered form. Caregivers mix powdered formula with water to prepare formula for infants to consume. While the FDA regulates the nutrient content of infant formula, there may be variability in formula intake with differences in formula preparation by caregivers and feeding patterns.

### **2.2. Remote Food Photography Method**

The Remote Food Photography Method (RFPM) is used to measure energy and nutrient intake utilizing digital photography of food selection and plate waste to estimate food intake. When using the RFPM, individuals use Smartphones to capture images of their food selection and plate waste. The images are then sent to study staff using a wireless network. Food images are stored in a computer program called the Food Photography Application. The food images acquired from digital photography are compared to known portion sizes of those food images to estimate energy and nutrient intakes. The use of digital photography and the RFPM has been validated in adults and can be readily adapted to other populations including infants and toddlers.

### **2.3. Summary**

Food intake is crucial during the first two years of life because it is a time of constant growth and development. Measuring food intake in infants is challenging due to constant changes in eating patterns and large variability in

food selection. Establishing accurate methods to estimate food intake in infants is important for establishing effective feeding practices, supporting adequate growth and development and to help understand the role of food intake in the development of childhood obesity. Digital photography and the RFPM is used to measure energy and nutrient intake in adults, but these methods have not been used to measure energy and nutrient intake in infants from birth to 12 months. The primary objective of this study is to determine the reliability and validity of the RFPM to assess food intake in formula fed infants.

## **2.4. Study Aims**

**Primary Aim:** To assess if the RFPM can accurately estimate simulated food intake compared to the gold standard— directly weighed foods.

**Secondary Aim:** To evaluate the inter- and intra-individual variability in infant formula preparation.

**Exploratory Aim:** To investigate the variability in infant formula preparation between caregivers and non-caregivers of infants. A caregiver will be defined as an individual who is a parent, grandparent, sibling, aunt or uncle, or nanny or babysitter who has provided care to an infant within the last 12 months.

## **3. RESEARCH DESIGN**

This is an observational study with the overall objective to determine the reliability and validity of the RFPM to assess food intake in formula fed infants.

## **4. STUDY POPULATION**

### **4.1. Participants**

Up to 75 men and women will be recruited to participate in a 2-week pilot study involving infant formula preparation. Participation is open to all adult individuals.

### **4.2. Eligibility Criteria**

Participants are eligible to participate in this study if they are:

- ≥ 18 years of age
- Willing to complete 2 study visits at Pennington Biomedical (PBRC)

## **5. RECRUITMENT**

Subjects will be recruited from within PBRC and the Greater Baton Rouge Area using the PBRC website advertisement and an email blast to Pennington Biomedical employees and Recruiting list serv.

## **6. ASSESSMENT SCHEDULE AND PROCEDURES**

Potential participants will complete a telephone or email screen to determine basic eligibility prior to enrollment. After signing the study consent and HIPAA authorization, participants will be required to complete 2 study visits separated by about 1 week (5-10 days). Study visits can be performed at any time of the day although the time of day will be standardized for each participant. Participants will complete several procedures during the study visits. See Table 1, Schedule of Procedures.

| Table 1: Schedule of Procedures | Screening        | Testing |         |
|---------------------------------|------------------|---------|---------|
|                                 | Telephone Screen | Visit 1 | Visit 2 |
| Eligibility Evaluation          | X                |         |         |
| Informed Consent and HIPAA      |                  | X       |         |
| Anthropometry (Height/Weight)   |                  | X       |         |
| RFBM Training                   |                  | X       |         |
| Infant Formula Preparation      |                  | X       | X       |
| Remote Food Photography Method  |                  | X       | X       |
| Directly Weighed Food Method    |                  | X       | X       |

### 6.1. Telephone Screen

A brief telephone interview will be used to describe the study and determine basic eligibility criteria (e.g. Age, BMI, Sex, Race). Interested and eligible subjects will be assigned a subject identification number (PBRC ID number) and scheduled for Visit 1. An email interview may be used to determine basic eligibility criteria if necessary. Where possible, the study informed consent form will be emailed to eligible subjects with intent for the participant to read and review the informed consent form prior to Visit 1.

### 6.2. Visit 1

Volunteers will report to PBRC Outpatient Clinic and Ingestive Behavior Laboratory (IBL) to complete Visit 1. Upon arrival, potential participants will read and review the informed consent form. After all questions and concerns are addressed and prior to study procedures being conducted, interested participants will provide written informed consent and will sign the HIPAA form. Body weight and height will be measured and body mass index will be calculated according to the standard procedures of PBRC. Participants will be asked to complete a questionnaire to assess parent/caregiver status. The questionnaire can be found in Appendix 1. The questionnaire is expected to take up to 5 minutes to complete. After completing the self-reported questionnaire, participants will be trained to use RFBM to capture photos.

Each participant will, in random order, prepare 2 bottles of infant formula measuring 2 fluid ounces, 4 fluid ounces, 6 fluid ounces, and 8 fluid ounces. A total of 8 formula bottles will be prepared at Visit 1. Manufacturers' instructions state that 1 level scoop of powdered formula (8.8g) yields a 2 fluid ounce bottle, 2 unpacked level scoops of powdered formula (17.6g) yields a 4 fluid ounce bottle, 3 unpacked level scoops of powdered formula (26.4g) yields a 6 fluid ounce bottle, and 4 unpacked level scoops of powdered formula (35.2g) yields an 8 fluid ounce bottle. The Remote Food Photography Method and Directly Weighed Food Method will be utilized for each formula preparation as described below. Food weights (to the nearest tenth of a gram) will be measured using METTLER TOLEDO PB3001 scales. For each bottle, the participant will use the formula scoop provided to measure the required amount of powdered formula. The participant will dispense the correct number of scoops of powdered formula into the formula bottle depending on which size bottle is being prepared. After all powdered formula is dispensed into the clear formula bottle, the participant will capture a photo of the formula bottle with powdered formula only. This will be referred to as food provision. PBRC staff will weigh the formula bottle with powdered formula only. The participant will pour water into the bottle and mix the formula. Then, the participant will capture a photo of the prepared formula bottle. This will also be called food provision. PBRC staff will weigh the prepared formula bottle. Then, the PBRC staff will discard a random amount of the prepared formula. The participant will capture a photo of the formula bottle after the random amount of the prepared formula has been discarded. This will be referred to as waste. Then, PBRC staff will weigh the formula bottle. The captured photos will be used to determine if the RFBM accurately estimates simulated infant food intake.

which will be evaluated as food provision minus waste. This procedure will be repeated to assess intra-individual variability.

### **6.3. Visit 2**

Participants will be asked to return to the IBL approximately 5 to 10 days later to complete Visit 2. At Visit 2, participants will be instructed to repeat the infant formula preparations from Visit 1. Participants will prepare 4 formula bottles at Visit 2. Each participant will, in a random order, prepare bottles that will provide 2 fluid ounces, 4 fluid ounces, 6 fluid ounces, and 8 fluid ounces of infant formula bottles.

## **7. MEASURES AND OUTCOME ASSESSMENTS**

### **7.1. Anthropometrics**

Height and body weight will be measured at Visit 1 using standard procedures of PBRC. Non-fasting body weight will be recorded. Body mass index will then be calculated from the recorded height and body weight.

### **7.2. Self-Report Questionnaires**

A questionnaire that will assess parent/caregiver status will be administered to the participants at Visit 1 (Appendix 1). The questionnaire will assess demographic information and parent/caregiver status. A caregiver will be defined as an individual who is a parent, grandparent, sibling, aunt or uncle, or nanny or babysitter who has provided care to an infant within the last 12 months. A log will be kept throughout the study to document the distribution of caregiver status among participants. Effort will be made to maintain balance between the number of caregivers and the number of non-caregivers participating in the study.

### **7.3. Remote Food Photography Method**

The RFPM procedures are detailed in the Background and Significance Section. In brief, participants will use RFPM to capture images of the powdered formula in the bottle, the prepared formula bottle, and the formula bottle after discarding waste.

### **7.4. Directly Weighed Food Method**

The directly weighed food method is a useful method for estimating food intake and simulated waste in research and clinical settings. The formula bottle with powdered formula, the prepared formula bottle, and the formula bottle after discarding waste will be directly weighed to the tenth of a gram using METTLER TOLEDO PB3001 scales in the IBL.

## **8. PARTICIPANT SAFETY AND CONFIDENTIALITY**

### **8.1. Risks To Participant**

This study does not involve major risk to participants. Efforts to minimize the potential risks of the assessment methods and outcome variables include frequent monitoring by the investigators. The study procedures include:

- Body weight. There is no risk to participants who record their body weight.
- Height. There is no risk to participants who record their height.
- Self-report Questionnaires. There are no anticipated risks from completing self-report questionnaires. It is estimated that the questionnaires will take 5 minutes to complete.
- Formula Preparation. There is no risk to participants who prepare formula.

### **8.2. Adverse events**

Serious adverse events in this study are defined to include: death, a life-threatening adverse experience, inpatient hospitalization or prolongation of existing hospitalization, a persistent or significant

disability/incapacity. In this study, an adverse event or experience is defined as any health-related unfavorable or unintended medical occurrence that happens after screening. AE data will be analyzed quarterly, but serious or life-threatening adverse events require immediate reporting and follow-up. We anticipate most adverse events will be mild and the participant will be able to resume activities within a day or two of reporting the event. Adverse Event reporting will follow the requirements of the IRB of the Pennington Biomedical Research Center. Serious adverse events will be reported within 48 hours. Other adverse events that are not serious but are unexpected and are associated with the study procedures will be reported within 10 days.

### **8.3. Confidentiality**

All volunteers are assured of their anonymity and confidentiality both verbally and in the informed consent form. The clinical facilities are strictly limited to the staff of the research institution and to research volunteers. This is accomplished by a variety of stringent security measures. All medical records are stored in locked areas. Access to these areas is limited to the clinical support staff, director of the clinical facilities, and the PIs. Volunteers' medical records are filed according to ID numbers. All forms on the chart, with the exception of consent form, display only the ID number. Electronic data storage is similarly restricted with only the PIs and authorized persons having access to databases containing confidential clinical records, i.e. those containing name, social security number, or other identifying information.

Data, including body weight and some demographic information will be collected from participants. Data are confidentially collected from study participants and are only used for research purposes. All records are kept in locked file cabinets, and participant data can be identified only by number. Data are used only in aggregate, and no identifying characteristics of individuals are published or presented.

## **9. DATA ANALYSIS PLAN**

### **9.1. Power Analysis**

We will test the primary aim to assess if the RFPM can accurately estimate simulated food intake compared to the gold standard— directly weighed foods. Power calculations were performed on the main outcome variable, which is the simulated food intake. Two measures of food provision will be obtained: powdered formula and prepared formula, the latter of which is created by adding water to the powdered formula. Food waste is defined as the liquid formula remaining in a bottle after simulating feeding (random discard of 10-90% of prepared bottle). Food intake is food provision minus food waste. A secondary aim is to evaluate the inter- and intra- individual variability in infant formula preparation so this study is also appropriately powered to detect differences in the grams of powdered dry formula in the bottle.

A power analysis was conducted for the Bland and Altman procedure that will be used to determine if the RFPM significantly over or underestimates food provision, waste, or intake and if the error associated with the RFPM varies over the amount of food provision, waste, and intake. Determining if error variance differs over levels of intake is critical to examining validity and accuracy; hence, the sample size was established based on the regression analysis used to do so since it required the largest number of participants.

A power analysis was conducted for the Bland-Altman regression analysis. The power analysis indicated that an  $R^2$  of .14 can be detected with 53 participants (power = .80) and this is considered acceptable based on studies that used Bland-Altman analysis on biological parameters. This research indicates that poor measures frequently have  $R^2 \geq 0.16$ ; therefore, sample size of 53 would yield satisfactory statistical power in the analyses for the primary aim. The primary aim was used for power calculations since sample size was based on the least powered endpoint (i.e. aim 1).

Paired dependent t-tests will determine if the RFPM has significant error; i.e., if RFPM estimates differ significantly from weighed food. Variance estimates for the power analyses were obtained from our laboratory [10] and assumptions included alpha equal to 0.05, two-tailed tests, and anticipated sample size with 5% attrition (56 subjects will begin the study anticipating we will have a final sample size of 53 subjects.) Again, power of .80 was considered acceptable.

Power for intake (provision minus waste) of prepared formula was calculated with variance estimates for intake of beverages from our laboratory. As illustrated in Table 2, with 53 participants and the assumptions listed above, we have 80% power to detect a 4.95 g difference between RFPM estimated and directly weighed prepared formula intake.

| Table 2. Effect Size Calculations for Intake (Provision minus Waste) of Beverages |                                                     |        |       |             |
|------------------------------------------------------------------------------------------|-----------------------------------------------------|--------|-------|-------------|
| n per group                                                                              | Minimum detectable difference in formula weight (g) | SD (g) | Power | Effect Size |
| 30                                                                                       | 6.80                                                | 9.71   | 0.80  | 0.70        |
| 40                                                                                       | 5.83                                                | 9.71   | 0.80  | 0.60        |
| 45                                                                                       | 5.44                                                | 9.71   | 0.80  | 0.56        |
| 50                                                                                       | 5.15                                                | 9.71   | 0.80  | 0.53        |
| 53                                                                                       | 4.95                                                | 9.71   | 0.80  | 0.51        |
| 55                                                                                       | 4.86                                                | 9.71   | 0.80  | 0.50        |
| 60                                                                                       | 4.66                                                | 9.71   | 0.80  | 0.48        |

With 53 subjects, we can detect a difference of 2.57 g (effect size or ES = 0.55, Table 3) between the RFPM's estimate and the weighed value for provision of powdered infant formula. This power analysis relied on variance estimates for condiments from our laboratory [10] which are similar to infant formula. This effect size of 2.57 grams reflects a very small amount of formula, indicating that the study is sufficiently powered. We recognize that predicting that no significant differences will be detected is problematic, though the proposed sample size and data analytic plan represents a viable alternative to equivalence tests that require very large sample sizes.

| Table 3. Effect Size Calculations for Food Provision (Dry Weight) |                                                     |        |       |             |
|--------------------------------------------------------------------------|-----------------------------------------------------|--------|-------|-------------|
| n per group                                                              | Minimum detectable difference in formula weight (g) | SD (g) | Power | Effect Size |
| 30                                                                       | 3.51                                                | 4.68   | 0.80  | 0.75        |
| 40                                                                       | 3.00                                                | 4.68   | 0.80  | 0.64        |
| 45                                                                       | 2.81                                                | 4.68   | 0.80  | 0.60        |
| 50                                                                       | 2.62                                                | 4.68   | 0.80  | 0.56        |
| 53                                                                       | 2.57                                                | 4.68   | 0.80  | 0.55        |
| 55                                                                       | 2.53                                                | 4.68   | 0.80  | 0.54        |
| 60                                                                       | 2.39                                                | 4.68   | 0.80  | 0.51        |

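### Tables 2 and 3 of the power analysis do not give the detectable differences of the planned paired t-test, and the SD they rest on is not defined

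*Protocol*

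**What the plan says.** Section 9.1 of the protocol names the test: "Paired dependent t-tests will determine if the RFPM has significant error; i.e., if RFPM estimates differ significantly from weighed food". Section 9.2 repeats it. The power assumptions are given once for these calculations: "assumptions included alpha equal to 0.05, two-tailed tests, and anticipated sample size with 5% attrition", with "Again, power of .80 was considered acceptable". The sample is a single one: "56 subjects will begin the study anticipating we will have a final sample size of 53 subjects".

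Two detectable differences follow. For intake of prepared formula (Table 2), "we have 80% power to detect a 4.95 g difference between RFPM estimated and directly weighed prepared formula intake"; the table shows SD 9.71 g and effect size 0.51 at 53. For provision of powder (Table 3), "With 53 subjects, we can detect a difference of 2.57 g (effect size or ES = 0.55, Table 3"; the SD is 4.68 g. In both tables the sample-size column is labelled as a number per group and the power column reads 0.80 in every row.

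The SD in Table 2 was "calculated with variance estimates for intake of beverages from our laboratory", and the SD in Table 3 came from the same laboratory's data on condiments. The protocol does not say whether either is the SD of the difference between the two methods or the SD of one method's values.

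The sample size of 53 is attributed to a different calculation, the Bland-Altman regression with R² = 0.14.

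**The concern.** Each bottle is assessed by photograph and by scale, so the comparison is within bottle and there are no groups to count. A per-group column suggests that the pairing was left out of the calculation.

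The tables also disagree with each other. With the test, n, alpha, sidedness and power fixed, the detectable difference in units of the SD of differences is one number, whatever the endpoint. The tables give two numbers in each of the seven rows: 0.70 and 0.75 at n = 30, 0.51 and 0.55 at n = 53, 0.48 and 0.51 at n = 60. Gaps of 0.03 to 0.05 are too large for rounding to two decimals.

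The figures carry some weight. Section 9.1 concedes that predicting a non-significant result is awkward, sets no equivalence test, and points to the smallness of 2.57 g as a sign of adequate power. A reader who wants to know what a non-significant t-test would rule out has only these two figures to go on.

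**Working it through.** **Inputs (section 9.1).** n = 53; two-sided alpha 0.05; power 0.80; SD 9.71 g (Table 2) and 4.68 g (Table 3); stated differences 4.95 g and 2.57 g.

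**Formulas.** Power from the noncentral t, with d = difference / SD:
- paired test: n − 1 degrees of freedom, noncentrality d√n, where the SD is that of the paired differences;
- two independent groups of n: 2n − 2 degrees of freedom, noncentrality d√(n/2);
- paired test with a per-method SD and correlation ρ: SD of differences = SD × √(2(1 − ρ)).

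**Step 1: the plan's own effect sizes.** 4.95/9.71 = 0.510 and 2.57/4.68 = 0.549. Each table divides the difference by its own SD correctly.

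**Step 2: effect size detectable with 80% power.**

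| n | Table 2 | Table 3 | Paired | Two groups |
|---|---|---|---|---|
| 30 | 0.70 | 0.75 | 0.529 | 0.736 |
| 40 | 0.60 | 0.64 | 0.454 | 0.634 |
| 45 | 0.56 | 0.60 | 0.427 | 0.597 |
| 50 | 0.53 | 0.56 | 0.404 | 0.566 |
| 53 | 0.51 | 0.55 | 0.392 | 0.549 |
| 55 | 0.50 | 0.54 | 0.385 | 0.539 |
| 60 | 0.48 | 0.51 | 0.368 | 0.516 |

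Table 3 follows the two-group column. At n = 53 it is reproduced exactly (0.5493 × 4.68 = 2.57 g), and the other rows lie within 0.015. Table 2 follows neither column.

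**Step 3: power at the tabulated differences.**

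| | Two groups, n = 53 | Two groups, all rows | Paired, n = 53 | Paired, all rows |
|---|---|---|---|---|
| Table 2 | 73.9% | 73.9–76.0% | 95.4% | 95.4–96.0% |
| Table 3 | 80.0% | 79.2–81.5% | 97.5% | 97.3–97.8% |

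The paired columns take the tabulated SDs as SDs of differences.

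**Step 4: the n = 53 row for the planned test.** If the SDs are SDs of differences, 0.3921 × 9.71 = 3.81 g and 0.3921 × 4.68 = 1.84 g. If they are per-method SDs, multiply by √(2(1 − ρ)):

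| ρ | Factor | Intake | Powder |
|---|---|---|---|
| 0 | 1.414 | 5.38 g | 2.60 g |
| 0.5 | 1.000 | 3.81 g | 1.84 g |
| 0.9 | 0.447 | 1.70 g | 0.82 g |

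**Step 5: the correlation that would produce the printed figures.** Setting √(2(1 − ρ)) = tabulated effect size / paired effect size gives ρ = 1 − (0.51/0.392)²/2 ≈ 0.15 for Table 2 at n = 53, and ρ ≈ 0.02 for Table 3. Over all rows the range is about 0.13 to 0.16 for Table 2 and about 0 to 0.04 for Table 3.

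**Step 6: the basis of n = 53.** For R² = 0.14 with one predictor, the noncentrality is 53 × 0.14/0.86 = 8.63 on 1 and 51 degrees of freedom, and power is 82.2%. Attrition: 53/0.95 = 55.8, hence 56. Both statements hold.

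**The case against.** The strongest defence is that the SDs may be per-method SDs. The tabulated effect size is then the difference over a per-method SD, and a paired test can give different values for two endpoints with different correlations. The two tables would not strictly contradict each other. The fit is also not bad: with ρ = 0.14 the paired formula returns Table 2 to two decimals in six of seven rows (the exception is n = 30, 0.694 against 0.70), and with ρ = 0 it returns Table 3 in five of seven.

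What stands is that a flat contradiction between the tables cannot be proved from the protocol. The defence does not rescue the figures. It needs two different correlations, neither stated, both close to zero, between a photograph and a scale reading of the same bottle. That is implausible for a method expected to prove valid. A paired test with ρ = 0 also differs from the two-group test only in its degrees of freedom, so this route too takes almost no credit for pairing. It leaves the per-group label unexplained as well.

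It can also be said that 2.57 g is not an arithmetic slip. That is right: it is the correct answer for two independent groups, which is not the planned design.

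A reader might go further and infer that the study is underpowered or that 53 is the wrong number. The protocol does not support this. It takes 53 from the regression, where the figure holds, and if the SDs are SDs of differences the printed figures understate the power of the t-tests. Nor does any accuracy margin rest on these tables, since the protocol sets none.

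**Conclusion.** The point holds as a mismatch between the stated test and the stated figures. Table 3 gives the two-group result. Table 2 matches neither the two-group formula nor the paired formula with an SD of differences. The 80% power attached to 4.95 g and 2.57 g is therefore not supported for the paired t-test as described.

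It is tempting to say that the correct values are 3.81 g and 1.84 g. That holds only if 9.71 g and 4.68 g are SDs of paired differences, which the protocol does not say. On the per-method reading, for correlations from 0 to 0.9, intake runs from 5.38 g down to 1.70 g and powder from 2.60 g down to 0.82 g. The direction of the error therefore depends on the missing definition: the printed figures are too large for most of that range and slightly too small when the correlation is near zero.

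Severity is moderate to minor. The sample size, endpoints and analysis are unaffected; what changes is how a non-significant t-test can be read.

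**What to change.** In section 9.1:

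1. Recompute every row of Tables 2 and 3 for the paired t-test and relabel the first column as number of participants.
2. Check the source of 9.71 g and 4.68 g, and state whether each is an SD of the photo-minus-weighed difference or a per-method SD. If per-method, give the correlation used and the reason for it.
3. Correct the sentences that quote 4.95 g and 2.57 g. If the SDs are SDs of differences, the n = 53 row becomes 0.39 SD, that is 3.81 g for intake and 1.84 g for powder. Do not enter these values until step 2 has been settled.

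The cost is two tables, two sentences and one look at the source data. The sample size stays at 53 evaluable participants, with 56 starting.

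### The 2.57 g detectable powder error is treated as negligible, yet it is 7% to 29% of the powder in this study's bottles, so the stated adequacy of power for powder is unsupported

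*Protocol*

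**What the plan says.** Section 9.1 reports the sensitivity for powder provision: "With 53 subjects, we can detect a difference of 2.57 g (effect size or ES = 0.55, Table 3"). The SD behind it is 4.68 g, and its source is given as follows: "This power analysis relied on variance estimates for condiments from our laboratory [10] which are similar to infant formula". The section then concludes: "This effect size of 2.57 grams reflects a very small amount of formula, indicating that the study is sufficiently powered". No acceptable error, in grams or as a percentage, is given to support that judgement.

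The next sentence of 9.1 concedes that predicting a non-significant result is problematic, and puts forward the sample size and analysis plan as a workable alternative to equivalence tests.

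Two other places bear on whether 2.57 g is small. Section 6.2 (Visit 1) gives the label powder weights, beginning with "1 level scoop of powdered formula (8.8g) yields a 2 fluid ounce bottle" and rising in equal steps to 35.2 g for 8 fl oz. Section 2.1 reports from an earlier study that weighed food came within 5% of estimated energy requirements, whereas "24 hour dietary recalls overestimated energy intakes in infants by 13% and in toddlers by 29" per cent.

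**The concern.** The inference that power is sufficient is drawn directly from 2.57 g being negligible. The smallest bottle contains a single 8.8 g scoop, so 2.57 g is 0.29 of all the powder in it. A single gram figure across a four-fold range of bottle sizes also means very different accuracy at each size.

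Because the plan forgoes an equivalence test, a non-significant t-test for powder will be read as a sign that the photographic method is accurate. That reading is only as good as the sensitivity of the test, and for mean powder error the 2.57 g figure is the only sensitivity stated. If 2.57 g is not small relative to what is measured, the reassurance fails, most clearly for the small bottles.

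**Working it through.** **Inputs.** From section 9.1: n = 53, SD 4.68 g, detectable difference 2.57 g; "assumptions included alpha equal to 0.05, two-tailed tests, and anticipated sample size with 5% attrition"; "Again, power of .80 was considered acceptable". From section 6.2: label powder weights of 8.8, 17.6, 26.4 and 35.2 g. From section 2.1: 5% and 13% as reference points.

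**Step 1: reproduce the plan's figure.** Detectable difference = d × SD, where d gives 80% power in a two-sided 5% t-test.

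- Two independent groups of 53 (noncentrality d√(n/2), 104 df): d = 0.549, and 0.549 × 4.68 = 2.57 g. This matches. The other rows of Table 3 agree with the same formula to within 0.07 g.
- One paired sample of 53 (noncentrality d√n, 52 df): d = 0.392, giving 1.84 g if 4.68 g is the SD of the paired differences.

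Table 3 therefore follows a two-sample formula, although 9.1 and 9.2 plan paired t-tests.

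**Step 2: express it as a share of label powder weight.**

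| Bottle | Powder (g) | 2.57 g | 1.84 g |
|---|---|---|---|
| 2 fl oz | 8.8 | 29.2% | 20.9% |
| 4 fl oz | 17.6 | 14.6% | 10.4% |
| 6 fl oz | 26.4 | 9.7% | 7.0% |
| 8 fl oz | 35.2 | 7.3% | 5.2% |
| Mean of four | 22.0 | 11.7% | 8.3% |

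The 2.57 g figure is above 5% at every size. It is above 13% at 2 and 4 fl oz, and below 13% at 6 fl oz, at 8 fl oz and at the mean.

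**Step 3: power against a proportional bias.** This assumes that an SD of 4.68 g applies at each size and that each size is tested separately. The protocol states neither.

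| Bias | Grams | Two-sample basis | Paired, SD of differences 4.68 g |
|---|---|---|---|
| 13% at 2 fl oz | 1.14 | 24% | 42% |
| 13% at 4 fl oz | 2.29 | 70% | 94% |
| 13% at 6 fl oz | 3.43 | 96% | >99% |
| 13% at 8 fl oz | 4.58 | >99% | >99% |
| 13% at the 22 g mean | 2.86 | 88% | 99% |
| 5% at the 22 g mean | 1.10 | 22% | 39% |

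**Step 4: if 4.68 g is instead the SD of each method's values.** The SD of the differences is then 4.68 × √(2(1 − r)), with r the correlation between the methods, which the protocol does not give. The paired detectable difference is 2.60 g at r = 0, 1.84 g at r = 0.5, 1.16 g at r = 0.8 and 0.82 g at r = 0.9. For the 2 fl oz bottle these are 29%, 21%, 13% and 9%.

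**Step 5: would the planned analyses show the problem?** A constant error in grams has zero slope against amount, so a Bland-Altman regression on the gram scale would not flag it. A t-test pooled over sizes gives one mean in grams. Neither shows that the same error is four times as large, proportionally, at 2 fl oz as at 8 fl oz (35.2/8.8 = 4).

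**The case against.** Several points on the other side stand.

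- **The sample size does not depend on this sentence.** Section 9.1 sets n = 53 on the Bland-Altman regression (R² of 0.14) and names simulated intake as the main outcome. A reader might infer that the whole study is undersized. The document does not support that; powder provision is a supporting calculation.
- **A detectable difference is not a tolerance.** A reader might infer that a 2.5 g mean error would pass as no error. It would not. With SD 4.68 g and n = 53, an observed mean error is significant beyond about 1.80 g on the two-sample basis (1.983 × 4.68 × √(2/53)), or 1.29 g on the paired basis (2.007 × 4.68/√53). A true 2.5 g bias would be detected with about 78% or 97% power respectively.
- **The percentages in section 2.1 are not accuracy criteria for this study.** They concern energy intake in infants and toddlers, and the 5% is measured against estimated requirements. Setting powder weight against them is an analogy. It would also be too broad to say that 2.57 g matches the cited recall errors: it exceeds the 13% infant figure at two sizes only and reaches the 29% toddler figure only at 2 fl oz.
- **The paired figure could be smaller still.** Step 4 shows this if the two methods are highly correlated.
- **Dependence of error on amount is already examined** by the planned regression, and further analysis detail may sit in an analysis plan not shown here. Step 5 gives the limit of the first part. On the second, the point is not an omission: it is a claim the protocol makes that its own scoop weights do not bear out.

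**Conclusion.** The concern holds as a fault in one stated justification, not in the sample size and not in the arithmetic of Table 3 on its own formula. The protocol presents 2.57 g as negligible and infers adequate power for powder, but that amount is 29%, 15%, 10% and 7% of label powder at 2, 4, 6 and 8 fl oz. These percentages use only figures in the protocol.

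The paired alternative of 1.84 g is conditional on 4.68 g being the SD of paired differences, and even then it is 21% of the smallest bottle. The power figures by size rest on a common SD, borrowed from condiments, and on separate tests by size. The claim is weakest for the 2 fl oz bottle. The point should be addressed because the plan relies on this kind of sensitivity where an equivalence test would otherwise stand.

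**What to change.** 1. In section 9.1, delete the sentence that calls 2.57 g small and concludes that power is sufficient.
2. In its place, state the detectable difference as a percentage of weighed powder for each bottle size. Compute it for the paired test, and say whether 4.68 g is the SD of paired differences or of single measurements.
3. In section 9.2, add an analysis of relative error (log ratio, or error as a percentage of the weighed amount), reported by bottle size, alongside the gram-scale t-tests and the Bland-Altman regression.

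The sample size stays at 53. The cost is a wording change and one further scale of analysis on data already being collected. The downside is a stated sensitivity that looks less favourable for the small bottles.
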